### Outcomes

The primary outcome measure is the proportion of participants engaged in MOUD care on the 34th day following hospital discharge. Engagement in MOUD care is defined as verifiable coverage with a prescribed MOUD on that 34th day regardless of the source of prescribed MOUD coverage (e.g., opioid treatment program, primary care, jail, etc.). Participants give appropriate permission for release of such data during informed consent procedures and/or during study follow-up visits. Other objective means of MOUD verification, such as bringing a prescription bottle with participant name and dates covered by the prescription can, also be used for primary outcome.

### Data for primary outcome

MOUD engagement on the 34th day post hospital discharge is collected by self-report verified with an objective data source (e.g., pill bottle, prescription record, provider confirmation upon release of information, etc.) or, in the absence of self-report, an objective data source is used for the primary outcome (e.g., electronic medical records, provider confirmation upon release of information, etc.).

**Secondary outcomes include**:

Proportion of participants that experience any treatment emergent AEs and SAEs (those developed after initiation of treatment) following hospital discharge.Proportion of participants engaged with MOUD 90- and 180-days following hospital discharge.Proportion of participants with positive urine drug test for opiates, fentanyl, and oxycodone 34-, and 90-, and 180-days following hospital discharge.Proportion of participants with self-reported non-prescribed opioid use 34-, and 90-, and 180-days following hospital discharge.Proportion of participants with self-reported hospital readmissions at the 34- and 90-day visits.Proportion of participants with self-reported ED visits at the 34- and 90-day visits.

**Exploratory outcomes include**:

Proportion of participants with positive urine drug test for illicit drugs 34-, and 90-, and 180-days following hospital discharge.Proportion of participants with self-reported non-prescribed drug use 34-, and 90-, and 180-days following hospital discharge.Change in ASI-Lite measures from baseline to 180 days.Proportion of participants with self-reported medical follow-up at the 34- and 90-day visits.Proportion of participants adherent to antibiotic for OUD-related infections (e.g., endocarditis or skin-soft tissue infections) (when applicable).Self-reported alcohol use 34-, and 90-, and 180-days following hospital discharge.Hospital length of stay (for both the index hospitalization and readmissions).Self-reported 180-day hospital readmission rates.Self-reported 180-day ED visit rates.All-cause mortality rates at 30-, 90- and 180-days following hospital discharge.Comparative cost-effectiveness of XR-BUP and other MOUD.Non-fatal opioid overdose rates (discharge to 34-day visit and since last study visit at the 90- and 180-day visits).Fatal opioid overdose rates up to the 180-day visit.Satisfaction with MOUD treatment 180 days following hospital discharge.Self-reported 34- and 90-day hospital readmission rates related to OUD.Self-reported 34- and 90-day ED visits related to OUD.Quality of life.Receipt of subsequent XR-BUP injections (among the XR-BUP group only).Receipt of other MOUD treatments during follow-up (e.g., XR-BUP in the control group, methadone or SL-BUP in the XR-BUP group).

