**Methods:**

Six U.S. hospitals with ACS capable of prescribing all MOUD (i.e., methadone, buprenorphine, and extended-release naltrexone) recruit and randomize hospitalized patients with OUD who have not been on MOUD in the fourteen days prior to hospitalization. TAU may consist of any MOUD other than XR-BUP. Participants randomized to XR-BUP may receive any MOUD throughout their hospital stay and receive a 28-day XR-BUP injection within 72-hours of anticipated hospital discharge. There is no intervention beyond hospital stay. Participants are followed 34-, 90-, and 180-days following hospital discharge. The primary outcome is engagement in any MOUD 34-days following hospital discharge, which we hypothesize will be greater in the XR-BUP group. Randomizing 342 participants (171 per arm) provides 90% power to detect difference in the primary outcome between groups with an odds ratio of 2.1. Safety, secondary, and exploratory outcomes include: adverse events, MOUD engagement on days 90 and 180, opioid positive urine drug tests, self-reported drug use, hospital readmissions and emergency department visits, use of non-opioid drugs, fatal and non-fatal opioid overdose, all-cause mortality, quality of life, and cost-effectiveness. Data are analyzed by intention-to-treat, with pre-planned per-protocol and other secondary analyses that examine gender as an effect modifier, differences between groups, and impact of missingness.

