**Participants are excluded from participation if**:

Anticipated hospital length of stay less than 24-hours as determined by the ACS.Affected by a serious medical, psychiatric, or substance use disorder that, in the opinion of the study physician, would make it unsafe to participate in the study or may prevent collection of study data. This may include:

Disabling terminal diagnosis for which discharge from hospital is not anticipated or for which hospice care is being sought.Severe alcohol or benzodiazepine use disorder that is anticipated to require complex medical detoxification which cannot be completed prior to randomization.

3.Taking a long-acting opioid other than buprenorphine (e.g., methadone, extended-release oxycodone, extended-release morphine) for each of the three days immediately preceding randomization.4.Liver enzyme tests (Aspartate Aminotransferase (AST), Alanine Aminotransferase (ALT)) more than 3 times upper limit of normal.5.Currently pregnant or breastfeeding.6.Known allergy to buprenorphine or components of FluidCrystal delivery system.7.Receipt of MOUD in the 14 days prior to hospitalization as maintenance treatment; however, patients may have received MOUD for withdrawal management during or prior to hospitalization at the time of enrollment.8.Are currently in jail, prison or other overnight facility as required by court of law and/or is considered a prisoner under local law or is under current terms of civil commitment or guardianship.9.Previously randomized as a participant in the study – individuals may only be enrolled and randomized once.

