**Exploratory measures**									
Healthcare and Services Utilization [36]						X	X	X	
Pain Assessment [37]		X				X	X	X	
Depression (PHQ-9) [38]		X				X	X	X	
Post-Traumatic Stress Disorder (PC-PTSD-5) [39]		X				X	X	X	
Quality of Life (WHOQOL-BREF) [40]		X						X	
Non-Fatal Opioid Overdose		X				X	X	X	
Fatal Opioid Overdose (collected on SAE form)			X^d^	X	X	X	X	X	
Addiction Severity Index-Lite (ASI-Lite) Drug and Alcohol Use [41]		X						X	
Post-Hospitalization Medical Appointment Follow-Up						X	X		
Antibiotic Adherence for OUD-Related Infections^i^						X	X		
Hospital Length of Stay					X	X	X	X	
Subsequent XR-BUP Injections (XR-BUP group only)						X	X	X	
Receipt of Other MOUD						X	X	X	

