**Administrative forms**									
Protocol Deviations									X
Missed Visit and Visit Documentation Form		X		X		X	X	X	

Notes: ^a^Can be completed at different time points; ^b^For XR-BUP only; ^c^Completed only if reaction noted upon injection site examination; ^d^AEs/SAEs collected only after the participant is randomized; ^e^At 180-days, only SAEs are collected; ^f^COWS is assessed twice (before and two-hours after XR-BUP initiation) for each participant randomized to XR-BUP group only; ^g^Completed a second time before treatment initiation if there are more than 7 days between screening/baseline and treatment initiation; ^h^Collected only once during these visits and not at each indicated time point; ^i^Completed only by participants discharged from the hospital on antibiotics for drug-related skin and soft-tissue infections

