### Sample size

342 participants will be randomized in a 1:1 ratio to XR-BUP or TAU. The power calculation assumes the 34-day engagement rate is 0.39 for TAU [22] and 0.60 for XR-BUP and that 15% of the primary outcome values will be missing and treated as “not engaged” for the primary analysis. In that scenario, 85% of patients will have the assumed rate (0.39 and 0.60 for TAU and XR-BUP, respectively) and 15% of patients in both groups will have a rate of 0.0. As such, the new engagement rates will be 0.3315 for TAU and 0.51 for XR-BUP.

A Cochran-Mantel-Haenszel test with continuity correction based on odds ratios (OR) of 2.1 assuming different engagement rates by site (6 sites with 34-day engagement rates of 0.29 up to 0.37 for TAU and 0.46 up to 0.55 for XR-BUP group) suggests that a total of 342 participants (171 participants in each group) need to be enrolled to have 90% power to detect a difference in the 34-day engagement rates between TAU and XR-BUP (two-sided test, alpha [false positive rate] = 0.05). Following a blinded interim analysis, the DSMB may recommend the protocol be amended to increase the number of subjects enrolled into the study.

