### Outcomes analyses

The primary analysis compares the two groups (TAU and XR-BUP) for the primary outcome (engagement in MOUD care on the 34th day following hospital discharge) using the Cochran-Mantel-Haenszel test stratified by hospital under the principle of intention-to-treat (ITT), i.e., participants are analyzed in the group to which they were randomized irrespective of whether they received their assigned treatment. An additional analysis may be performed using a per-protocol analysis population (i.e., according to the actual treatment received).

Supplementary analyses of the primary outcome will be performed as follows: (a) consider gender as an effect modifier, (b) add adjusters for possible differences between groups, and (c) adjust for missing outcome data. Logistic regression is used for (a) and (b) whereas analyses adjusting for missing outcome data will use inverse probability weighting (IPW).

Analyses of secondary outcomes, broadly, will have a form similar to analysis of the primary outcome, or outcomes measured at multiple time-points (e.g., engagement in OUD care at 34-, 90-, and 180-days) will use a mixed-effect analysis with a person-specific random effect to capture correlation of a person’s multiple time-points. The particular form of analysis, e.g., logistic regression vs. normal-errors regression, will depend on the outcome, and outcomes on continuous or effectively continuous scales may be transformed before analysis (e.g., by taking the logarithm) to allow use of analyses that assume normally distributed errors.

Analytic approaches for exploratory outcomes are similar to those described for the primary and secondary outcomes. In addition, we will explore moderators and mediators of MOUD engagement and other outcomes such as hospital length of stay and antibiotic completion rates (where appropriate). Potential moderators and mediators include hospital length of stay, post-hospital discharge medical follow-up, quality of life, depression, post-traumatic stress syndrome, pain, and treatment satisfaction.

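### All-cause mortality is timed from hospital discharge, so as worded it does not cover deaths between randomisation and discharge

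*Protocol article*

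**What the plan says.** All places are in the protocol article.

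- **Mortality outcome** (Exploratory outcomes): "All-cause mortality rates at 30-, 90- and 180-days following hospital discharge". No denominator is given.
- **Timing of treatment** (Abstract, Methods): XR-BUP participants "receive a 28-day XR-BUP injection within 72-hours of anticipated hospital discharge". The Intervention section says the same, and Table 1 sets the discharge date as day 0. Randomisation comes before both.
- **Safety outcome** (Secondary outcomes): the proportion with treatment-emergent AEs and SAEs. Treatment-emergent is defined as arising after treatment starts, but the outcome is also worded as following discharge.
- **Collection window** (Table 1, note d): "AEs/SAEs collected only after the participant is randomized". The AE/SAE row is marked from randomisation through the day-180 visit, with SAEs only at day 180. The fatal-overdose row uses the SAE form over the same span.
- **Fatal overdose outcome** (Exploratory outcomes): rates up to the 180-day visit, with no discharge start.
- **Analysis set** (Outcomes analyses, for the primary outcome): "participants are analyzed in the group to which they were randomized irrespective of whether they received their assigned treatment". Analyses of exploratory outcomes are said to be similar.

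**The concern.** In a randomised comparison of deaths, the clock should start at randomisation, because only there are the arms alike by design. Discharge comes later, and its timing could differ by arm. The protocol itself lists index length of stay as an exploratory outcome and as a possible moderator or mediator. An outcome that starts at discharge is silent about anyone who dies before reaching it. In the XR-BUP arm that includes the interval between injection and discharge.

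The definitions also disagree with each other. A fatal opioid overdose in hospital falls within the fatal-overdose outcome but outside all-cause mortality, so a subset could exceed its whole. A non-overdose death after injection and before discharge, read literally, enters neither the mortality outcome nor the AE/SAE outcome, although the SAE form records it. At stake is how complete and coherent the reported mortality comparison is.

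**Working it through.** **1. Origins and coverage, side by side.**

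| Item | Starts at | Covers randomisation to discharge? |
|---|---|---|
| SAE collection (Table 1, note d) | Randomisation | Yes |
| Fatal overdose, collection | Randomisation | Yes |
| Fatal overdose, outcome | No discharge start; ends at day-180 visit | Yes, as worded |
| All-cause mortality, outcome | Discharge | No, as worded |
| AE/SAE, secondary outcome | Worded as following discharge | No, as worded |

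The gap lies in the outcome definitions, not in the data.

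**2. Figures the plan states.** It gives no mortality rate or expected number of deaths for the trial. Its sample size is not in dispute. With 0.39 × 0.85 = 0.3315 and 0.60 × 0.85 = 0.51 (OR 2.10), the two-proportion formula with continuity correction (90% power, two-sided 0.05) gives 170 per arm, against the stated 171. Mortality plays no part in it.

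**3. Expected deaths after discharge.** The Background cites 8% all-cause mortality in the year after discharge. Assume a constant hazard and that this rate applies here:

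F(t) = 1 − 0.92^(t/365), expected deaths = 342 × F(t)

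| Day | F(t) | Deaths of 342 |
|---|---|---|
| 30 | 0.68% | 2.3 |
| 90 | 2.03% | 7.0 |
| 180 | 4.03% | 13.8 |

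If the hazard were halved, the day-180 count would be 342 × (1 − 0.92^(90/365)) = 7.0.

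**4. Effect of an in-hospital death.** With k such deaths in an arm of 171, and F = 4.03% by day 180 after discharge among those discharged alive:

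rate from randomisation = [k + (171 − k) × F] / 171

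| k | Rate |
|---|---|
| 0 | 4.0% |
| 1 | 4.6% |
| 2 | 5.2% |
| 3 | 5.7% |
| 5 | 6.8% |

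Each death adds (1 − 0.0403)/171 = 0.56 points; the upper bound is 1/171 = 0.58.

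**5. How many there might be.** The documents do not say. If 0.3% to 1% of those randomised died before discharge (an assumption), that is 342 × 0.003 = 1.0 to 342 × 0.01 = 3.4 deaths, against 2.3 expected in the first 30 days after discharge. That comparison depends entirely on the assumed range.

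**The case against.** **Discharge is a sensible anchor.** The research question is the move from hospital to community care, and every visit is timed from discharge. This stands as a reason to keep the post-discharge rates. It does not supply a rule for deaths before discharge.

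**The gap is small.** Injection is planned within 72 hours of anticipated discharge, so the planned post-injection interval is at most about three days. The physician may also exclude participants with a "Disabling terminal diagnosis for which discharge from hospital is not anticipated or for which hospice care is being sought". Both points stand and lower the expected count. The interval from randomisation to injection can be longer, however, and it applies to both arms.

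**The deaths are not lost.** A reader might infer that participants who die in hospital are dropped and that the comparison is not intention-to-treat. The documents do not say so: no denominator is stated, the deaths are recorded as SAEs, and the analysis is by randomised arm. The supported statement is narrower, namely that the outcome as worded does not cover these deaths.

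**Missing-data analyses.** A reader might also infer that deaths would be coded as missing and then weighted away in the inverse probability weighted analysis, or modelled as survivors in the mixed models. The documents do not support this.

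- The sample-size assumption that "15% of the primary outcome values will be missing and treated as “not engaged” for the primary analysis" does not mention death.
- Engagement is defined as verifiable coverage on the day, and an objective source may settle it without self-report, so a known death can be an observed non-engagement.
- Weighting is planned only for the day-34 primary outcome. Even if deaths were coded as missing there, the effect would be negligible. With 0.77% dead by day 34 in each arm, counting them as not engaged gives 0.387 v 0.595 (difference 0.208, OR 2.33). Excluding them gives 0.39 v 0.60 (difference 0.210, OR 2.35).
- How death is coded in such models is commonly left to the analysis plan, which is not shown.

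**Conclusion.** The point holds for the time origin of all-cause mortality. The outcome is anchored to a post-randomisation event and, as worded, leaves deaths between randomisation and discharge uncovered. It also does not match the collection of SAEs and fatal overdoses from randomisation, or the fatal-overdose outcome. The secondary AE/SAE outcome has similar wording.

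The size is about 0.6 percentage points on an arm's mortality per in-hospital death. The number of such deaths is unknown from the documents and probably small. The 4% comparison figure rests on the cited 8% yearly mortality, a constant hazard, and its applicability to people starting treatment.

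This is a minor improvement to an exploratory outcome. The primary Cochran-Mantel-Haenszel test, the sample size and the power do not change, and no criticism of the weighting or mixed-model analyses follows from it.

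**What to change.** In the outcome definition, or in the analysis plan if it is still open:

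1. Report all-cause mortality from randomisation in all randomised participants, by assigned arm.
2. Keep the 30-, 90- and 180-day post-discharge rates as a second display, with the denominator stated.
3. Use the same origin for all-cause mortality and fatal opioid overdose, so that every overdose death is also counted as a death.
4. State whether the secondary AE/SAE outcome is meant to leave out events between start of treatment and discharge, and if not, align its wording with the collection window.

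The cost is a few sentences. Deaths are already recorded on the SAE form from randomisation, so no new data, visits or participants are needed.

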### Sample size

342 participants will be randomized in a 1:1 ratio to XR-BUP or TAU. The power calculation assumes the 34-day engagement rate is 0.39 for TAU [22] and 0.60 for XR-BUP and that 15% of the primary outcome values will be missing and treated as “not engaged” for the primary analysis. In that scenario, 85% of patients will have the assumed rate (0.39 and 0.60 for TAU and XR-BUP, respectively) and 15% of patients in both groups will have a rate of 0.0. As such, the new engagement rates will be 0.3315 for TAU and 0.51 for XR-BUP.

A Cochran-Mantel-Haenszel test with continuity correction based on odds ratios (OR) of 2.1 assuming different engagement rates by site (6 sites with 34-day engagement rates of 0.29 up to 0.37 for TAU and 0.46 up to 0.55 for XR-BUP group) suggests that a total of 342 participants (171 participants in each group) need to be enrolled to have 90% power to detect a difference in the 34-day engagement rates between TAU and XR-BUP (two-sided test, alpha [false positive rate] = 0.05). Following a blinded interim analysis, the DSMB may recommend the protocol be amended to increase the number of subjects enrolled into the study.

### Outcomes analyses

The primary analysis compares the two groups (TAU and XR-BUP) for the primary outcome (engagement in MOUD care on the 34th day following hospital discharge) using the Cochran-Mantel-Haenszel test stratified by hospital under the principle of intention-to-treat (ITT), i.e., participants are analyzed in the group to which they were randomized irrespective of whether they received their assigned treatment. An additional analysis may be performed using a per-protocol analysis population (i.e., according to the actual treatment received).

Supplementary analyses of the primary outcome will be performed as follows: (a) consider gender as an effect modifier, (b) add adjusters for possible differences between groups, and (c) adjust for missing outcome data. Logistic regression is used for (a) and (b) whereas analyses adjusting for missing outcome data will use inverse probability weighting (IPW).

Analyses of secondary outcomes, broadly, will have a form similar to analysis of the primary outcome, or outcomes measured at multiple time-points (e.g., engagement in OUD care at 34-, 90-, and 180-days) will use a mixed-effect analysis with a person-specific random effect to capture correlation of a person’s multiple time-points. The particular form of analysis, e.g., logistic regression vs. normal-errors regression, will depend on the outcome, and outcomes on continuous or effectively continuous scales may be transformed before analysis (e.g., by taking the logarithm) to allow use of analyses that assume normally distributed errors.

Analytic approaches for exploratory outcomes are similar to those described for the primary and secondary outcomes. In addition, we will explore moderators and mediators of MOUD engagement and other outcomes such as hospital length of stay and antibiotic completion rates (where appropriate). Potential moderators and mediators include hospital length of stay, post-hospital discharge medical follow-up, quality of life, depression, post-traumatic stress syndrome, pain, and treatment satisfaction.

Cost-effectiveness analysis will be conducted from a health sector perspective over the 6-month trial participation time horizon as well as over a remaining lifetime time horizon (by extrapolating from trial outcomes). Costs will include the healthcare costs associated with the initial OUD management pre-discharge (either a single dose of XR-BUP or TAU) and post-discharge healthcare utilization (ED visits and hospitalizations) and OUD care in the first six-months. Post-discharge costs will be estimated by multiplying self-reported healthcare utilization by the relevant Centers for Medicare and Medicaid Services (CMS) reimbursement rates [42]. 

The effectiveness of the interventions will be assessed in terms of quality-adjusted life-years (QALYs), which reflect both length and quality of life. We will estimate the average QALYs accrued under each intervention by calculating the amount of time participants spend in different OUD states (based on reported ED use, hospitalizations, and OUD care in the first 6 months) multiplied by the health-related utility of that state estimated from published data [10, 43]. Mortality is accounted for by assigning death a utility value of zero.

For the lifetime time horizon analysis, costs and QALYs after 6 months will be estimated by extrapolating from trial outcomes using estimated OUD outcomes from the published literature, economic analyses of MOUD treatments, and OUD modeling studies. We will conduct sensitivity analyses to assess the sensitivity of our cost-effectiveness conclusions on any extrapolation assumptions.

Once costs and QALYs have been assessed for XR-BUP and TAU, we will compare the incremental costs and benefits of XR-BUP. If XR-BUP yields a health benefit (increase in QALYs) and is less expensive than TAU, we will calculate the extent of this cost-savings to the healthcare sector. If XR-BUP is more expensive, but also more beneficial, than TAU, we will calculate the incremental cost-effectiveness ratio (ICER) of XR-BUP, which is the additional cost of each additional QALY gained by using XR-BUP for hospital-initiated MOUD instead of TAU. Cost-effectiveness conclusions will depend on the value of the ICER. In the US, interventions with an ICER less than $100,000 per QALY gained are considered cost-effective, between $100,000 - $150,000 per QALY gained are considered marginally cost-effective, and over $150,000 per QALY gained is considered not cost-effective.

